The 28-day + 6-month extension period will include a subset of SCD patients who will receive three consecutive RCEs with study RBCs. For SCD patients undergoing regular RCE, the parameters listed in Table 2 should be assessed before and 15 min to 4 h after each RCE procedure. These assessments will be performed at 14-day (± 7 days) intervals between each of the 3 study RCE episodes.

Study RBC components will be ordered and administered to study patients by their treating physicians according to local standards of care. Randomized patients who do not receive any RBC transfusion within 28 days of randomization will be withdrawn and replaced. No additional data will be collected for these patients, who will not be included in the data analysis. These subjects may be reassessed for eligibility and re-enrollment after withdrawal.

If a subject is determined to have developed a treatment-emergent antibody to amustaline/GSH RBCs, the subject should be withdrawn from the active treatment phase of the study but should continue with all planned safety assessments per protocol. If the subject requires further transfusion, conventional RBC should be transfused. The subject should be actively investigated for signs or symptoms of intravascular or extravascular hemolysis for at least 4 weeks after the last study transfusion. Blood samples should be sent to the study’s central immunohematology reference center (Versiti Blood Center of Wisconsin, formerly Blood Center of Wisconsin) for assessment of the hemolytic potential and changing characteristics and titer of amustaline/GSH antibodies every 1–2 weeks for 4 weeks or until resolution of the event.

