Non-study RBCs received during the study transfusion period will be included in the calculation of Hb content transfused. For each non-study RBC component received, the Hb content will be imputed using the average Hb content per study RBC component from the Control group within each clinical site.

The treatment difference in the adjusted Hb increment will also be summarized descriptively (with a 95% confidence interval) as exploratory analyses for the following mITT subgroups:Repeatedly transfused non-bleeding patients (defined as non-bleeding patients who receive at least 3 study RBC episodes).Subgroup by clinical site, age group (< 18, 18–64, and ≥ 65 years old), sex, and race (e.g., white vs. other races), as appropriate.

For SCD patients enrolled in the 6-month extension for three RCE procedures, HbA clearance will be estimated from the area under the curve (AUC) calculated by the trapezoidal rule based on measurements from samples collected within 4-h of each RCE, on Day 14 (± 7-days) and prior to the next scheduled RCE. Values will be adjusted by the duration in days used to calculate the AUC (i.e., between the 15 min-to-4-h post-transfusion sample and pre-transfusion sample of the next transfusion) and averaged over all study RCE procedures for each patient.

For the secondary efficacy endpoint of Hb consumption, the analysis will be conducted only in non-bleeding mITT patients who participate in both of the initial 28-day and 6-month extension periods and will utilize integrated data from both periods. Treatment differences in non-bleeding mITT patients will be assessed using the same non-inferiority test methods described above for the primary endpoint analysis. Interaction terms between the treatment and covariates will be explored, as necessary. For the adjusted Hb consumption analysis, the upper bound of a two-sided 95% confidence interval for the treatment difference (Test – 1.15 × Control) less than or equal to zero will result in the rejection of inferiority null hypothesis and the conclusion of non-inferiority.

Adjusted Hb consumption will be calculated as total Hb mass transfused in grams divided by body weight in kg at baseline and duration of the study transfusion period in days (g/kg/day). The total Hb mass transfused is the sum of the Hb content for all study and non-study RBC components transfused during the study transfusion period (i.e., 28 days or 28-day + 6-months, unless subjects prematurely discontinue the study).

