For patients who prematurely discontinue from the study, the duration of the study transfusion period will be calculated as:

$$\left(end\;date\;of\;study\;transfusion\;period\right)-\left(start\;date\;of\;first\;study\;RBC\;component\right){+1}$$

Where the end date of the study transfusion period will be defined according to the following rules:For subjects who withdraw due to death, the date of death will be the end date of the study transfusion period.For patients withdrawn for reasons other than death (e.g., lost to follow-up, withdrawal of consent, AE), the last date of a study or non-study RBC transfusion during the planned study transfusion period (28-days or 28-day + 6-months) will be the end date of the study transfusion period.

The treatment difference in the adjusted Hb consumption will also be summarized descriptively as exploratory analyses for the following mITT subgroups:Repeatedly transfused non-bleeding patients (defined as non-bleeding patients who receive at least 3 study RBC episodes).Subgroup by clinical site, age group (< 18, 18–64, and ≥ 65 years old), sex, and race, as appropriate.

Only mITT patients will be included in the safety analysis. Treatment-emergent AEs are defined as AEs with an onset date/time that is on or after the start date/time of the first study RBC transfusion. AEs will be summarized by treatment group, system organ class (SOC), and preferred term as applicable. The proportion of patients with AEs possibly, probably, or definitely related to study RBC transfusion will be compared between treatment groups using a Cochran-Mantel–Haenszel (CMH) test (controlling for clinical site and baseline bleeding status). The risk difference associated confidence interval will also be reported. In the event of sparse counts, Fisher’s exact test may also be used to provide statistical interpretation.

To investigate the potential impact of irradiation, subgroup analysis by irradiation status (yes vs. no) may be presented for the primary efficacy endpoint and selected safety data (including SAEs, AEs, and potassium level).

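### Hb consumption: for withdrawals other than death the period ends at the last transfusion, so the rate is biased upward, and the death rule differs

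*Protocol article*

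**What the plan says.** All of this is in the protocol article, *Statistical methods*, unless stated otherwise.

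- The endpoint: "Adjusted Hb consumption will be calculated as total Hb mass transfused in grams divided by body weight in kg at baseline and duration" of the transfusion period in days. Study and non-study RBCs both count in the numerator.
- Completers have the planned length as denominator. "For patients who prematurely discontinue from the study, the duration of the study transfusion period will be calculated as" end date minus start date of the first study RBC component, plus 1.
- Deaths: "For subjects who withdraw due to death, the date of death will be the end date of the study transfusion period".
- Other withdrawals (loss to follow-up, withdrawn consent and adverse event are the examples given): the end date is "the last date of a study or non-study RBC transfusion during the planned study transfusion period".
- There is no minimum duration and no provision for a patient with a single transfusion.
- The analysis covers "non-bleeding mITT patients who participate in both of the initial 28-day and 6-month extension periods". Non-inferiority is concluded with "the upper bound of a two-sided 95% confidence interval for the treatment difference (Test – 1.15 × Control) less than or equal to zero", that is, a 15% margin.

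Under *Transfusion support periods*, a patient who develops an antibody to the Test cells is also taken off study RBCs: "the subject should be withdrawn from the active treatment phase of the study". Such a patient stays in safety follow-up and receives conventional RBCs if more are needed.

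**The concern.** A consumption rate should count the Hb given and the days over which it was enough. For non-death withdrawals the rule counts every transfusion but ends the clock on the day of the last one. The days which that last transfusion covered are discarded although they were observed. The denominator can never exceed the observed time, so the error goes in one direction only.

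The two kinds of early exit are also on different scales. Take two patients of equal weight, each given the same Hb mass on day 1 only, who both leave on day 21. The one who died has a duration of 21 − 1 + 1 = 21 days. The one who withdrew consent has 1 − 1 + 1 = 1 day, and a rate 21 times as high for the same history.

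The endpoint is secondary, but it has a formal non-inferiority rule on arm means. Inflated values raise the mean and the variance of whichever arm the withdrawals fall in.

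**Working it through.** The protocol gives no figure for this rule, so there is none to reproduce. It also gives no transfusion interval, no withdrawal rate and no variability for Hb consumption. Those are assumptions below.

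**Inputs**
- Duration formula, end-date rules and 15% margin: *Statistical methods*.
- T, the transfusion interval: assumed 14, 21 or 28 days. The cap of ten episodes (*Discussion*) over 28 days plus 6 months, about 211 days, gives 211/10 ≈ 21 days for a patient who uses all ten. This makes 21 plausible but does not state it.
- Patients per arm: *Sample size* aims for 140 extension subjects, up to 30 of them on red cell exchange. Exchange patients are classed as bleeding and so fall outside this analysis. That leaves about 140 − 30 = 110, or 55 per arm at 1:1.

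**Step 1. Inflation for one patient.** With k equal transfusions of mass m every T days, the steady rate is m/T. The rule gives km/((k−1)T+1). The ratio is

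kT / ((k−1)T + 1),

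which is above 1 whenever T is above 1 day.

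| T (days) | k = 1 | k = 2 | k = 3 | k = 5 |
|---|---|---|---|---|
| 14 | 14 | 1.87 | 1.45 | 1.23 |
| 21 | 21 | 1.91 | 1.47 | 1.24 |
| 28 | 28 | 1.93 | 1.47 | 1.24 |

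For k = 2 and T = 21: 42/22 = 1.91. For k = 1 the denominator is 1 day and the factor is T itself.

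**Step 2. Shift in the arm mean.** One patient inflated by a factor f moves a 55-patient mean by (f − 1)/55.
- k = 1: 13/55 = 24% (T = 14), 20/55 = 36% (T = 21), 27/55 = 49% (T = 28). With 70 per arm, the most that 140 subjects allow, the range is 13/70 = 19% to 27/70 = 39%.
- k = 2, T = 21: 0.91/55 = 1.7%. Five such patients in one arm: 5 × 0.91/55 = 8.3%.
- k = 3, T = 21: 0.47/55 = 0.9%.

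**Step 3. Effect on the test.** Simulation with 55 per arm, lognormal values, assumed CV 30%, T = 21 and no true difference:

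| Withdrawals other than death | Chance of concluding non-inferiority |
|---|---|
| none | 68% |
| one, k = 1, in Test | about 0% |
| one, k = 1, in Control | about 2% |
| one, k = 2, in Test | 54% |
| one, k = 2, in Control | 75% |
| five, k = 2, in Test | 12% |
| five, k = 2, in each arm | 45% |

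The 68% depends on the assumed CV: it is 83% at CV 25% and 31% at CV 50%.

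**Step 4. The other direction.** If Test truly consumes 15% more, one k = 2 withdrawal in Control raises the chance of wrongly concluding non-inferiority from 2.5% to about 4%. Five in Control raise that arm's mean by 8.3%, so a true ratio of 1.15 would appear as 1.15/1.083 = 1.06. The single-transfusion case does not work this way: in either arm it inflates the variance so much that the test almost never concludes non-inferiority.

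**The case against.** The strongest reply concerns the analysis population. The test is limited to patients who take part in both periods. If that means actually entering the extension, a patient who leaves within 28 days after one transfusion is not analysed. At a 21-day interval, a patient who reaches the extension would already have had a second transfusion on about day 22. The realistic worst case is then k = 2, at 1.9-fold and 1.7% of the arm mean. This stands as a limit on the extreme case, but the text does not settle it. Under *Screening/randomization*, consent for the extension is taken at initial enrolment, so participation could equally mean enrolment. A patient might also enter the extension without a second transfusion, and was then observed for more than 28 days, which makes the factor against observed time larger than 28.

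Non-study transfusions also move the end date, and an episode spread over two dates gives a denominator above one day. Both soften the extreme case. Neither removes the bias for larger k.

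A reader might infer that the rule biases against the Test arm, because antibody formation triggers withdrawal. The document does not support that. Those patients leave active treatment but remain in follow-up, and later conventional transfusions would extend their end date. Whether they count as having discontinued the study is not stated. The *Discussion* reports four reactive antibodies so far, with arms still blinded. Arm-related withdrawal is possible but not shown.

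**Conclusion.** The rule as stated gives too high a rate for every non-death withdrawal and is inconsistent with the rule for deaths. This follows from the formula and needs no assumption beyond transfusions being more than a day apart. The size does rest on assumptions: about 1.9, 1.5 and 1.2 for two, three and five transfusions at intervals of 14 to 28 days. One such patient matters little; several, if unequal between arms, materially distort the test in either direction.

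Three stronger readings should be avoided. An inflation of about 20-fold is not a general result: it is the assumed interval, and it applies only to a patient transfused on one date who is also in the analysis population. It would also be wrong to call this the only chronic-use efficacy endpoint, since HbA clearance over repeated exchange is another. Nor are the primary efficacy and safety endpoints affected, as they do not use this duration. It is a should-fix on a secondary endpoint.

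**What to change.** Before unblinding, define the end date for withdrawals other than death as the date of withdrawal or last contact, no later than the planned end of the transfusion period. Count Hb mass over that same window. In the same sentence, state whether taking part in both periods means enrolment in the extension or entry into it, and whether patients taken off study RBCs for an antibody count as discontinued.

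Do not instead keep the last transfusion as the end date and leave out that episode's Hb mass. A patient with one transfusion would then have 0 g over 1 day, a consumption of zero.

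The cost is a small change to the derivation and reliance on withdrawal or last-contact dates. Outpatient surveillance calls at least every 35 days and the assessments on early termination should supply them. The new rule does not make every short record reliable: a patient who leaves a few days after a transfusion still has a short denominator, as one who dies then does. The article says the study remains blinded and expects the last assessments in the third quarter of 2026, so the change can be made without appearing data-driven.

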### Interim review

After approximately 300 patients are treated and at any other time that safety or enrollment rate concerns arise, safety data will be summarized in a group blinded manner for the DSMB's interim safety data review. Enrollment and study transfusions will continue during the interim safety evaluation, unless otherwise advised by the DSMB. Depending on the group blinded safety data reviewed, the DSMB may call for an additional unscheduled review, request to see unblinding summary, and/or suggest holding, stopping, or modifying the study for safety concerns.

As this planned interim analysis can only stop the trial for safety concerns, no adjustments will be made for the alpha level. If the study is discontinued as a result of this interim safety review, unblinded safety and efficacy data will be analyzed then and submitted to the DSMB and FDA.

### Data and Safety Monitoring Board (DSMB)

Study data will be monitored on a regular basis by a DSMB that is independent of the Sponsor, funder (BARDA) and Investigators. The primary responsibility of the DSMB is to ensure patient safety. DSMB members will be independent of the Sponsor. The Sponsor will notify the DSMB of fatal outcomes assessed to be possibly, probably, or definitely related to a study RBC and any confirmed amustaline/GSH RBC antibodies within 72 h of becoming aware of the event. DSMB members will be selected based on relevant academic and real-world training and experience. The DSMB will include specialists in blood banking, immunology, biostatistics and clinical medicine. The work of the DSMB will be guided by a charter developed by the Sponsor and agreed by all members of the board.

## Discussion

Over the last decade epidemics of multiple vector-borne arboviruses (e.g., Dengue [DENV], Chikungunya [CHIKV] and Zika [ZIKV] viruses) with the potential for transmission via transfusion have emerged in several areas of the world [16]. ZIKV, in particular, has major implications for blood safety and availability [17] as it may be transmitted by transfusion [18–20] and has potential deleterious outcomes such as microcephaly [21, 22] and Guillain–Barre syndrome [23]. In 2016, FDA issued guidance recommending the cessation of blood collections in areas with active community transmission of ZIKV, such as Puerto Rico. Platelets and plasma could be collected if an approved pathogen reduction device was used [24]. The US Government response to the 2014–2016 ZIKV outbreak in the Americas also included funding for the amustaline/GSH PR-RBC study described here. Subsequent arboviral outbreaks and the COVID-19 pandemic have led to increasing interest in pathogen reduction technologies (PRT) for RBCs as an additional safety measure for blood components [25–31].

Pathogen reduction strategies are approved in the US for platelet and plasma components. Current strategies to reduce the risk of TTI for RBC components include only pre-donation evaluation and selection of low-risk donors followed by serologic and/or nucleic acid testing (NAT) for selected known infectious pathogens. Limits to the level of sensitivity achievable with current testing technologies and algorithms and emerging pathogens that may contaminate the blood supply for a period of time prior to discovery remain a concern [32, 33]. Approved tests are not available for all of the infectious agents known to contaminate blood components, and while bacterial culture screening systems are widely used for platelets (which can be derived from whole blood donations that also produce RBC and plasma components), RBC components are not routinely screened for bacterial contamination [32, 34–37]. Unlike infectious risks, TA-GVHD risk can be effectively mitigated by irradiation. However, approximately half of TA-GVHD cases occur in patients who do not qualify for irradiated blood products under current guidelines in Europe and North America, leading to substantial morbidity and mortality among impacted patients [38].

In this setting, the RedeS study aims to demonstrate the safety of amustaline/GSH PR-RBCs in subjects requiring acute and chronic transfusion support, including SCD patients undergoing RCE therapy. The ZIKV outbreak presented a unique opportunity to test the technology in an emergency use scenario in Puerto Rico where the virus was circulating in blood donors [29, 39, 40]. The waning of the ZIKV outbreak led to RedeS protocol amendments associated with broader subject enrollment strategies, notably the expansion to hospitals on the US mainland and Turkey, and the 6-month extension for subjects requiring chronic RBC transfusion support or for SCD patients undergoing repeated RCE procedures.

The primary endpoint, Hb increment, is the most commonly measured indirect indicator of response to transfusion and is widely used clinically to guide transfusion therapy decisions and assess transfusion response. Currently there are no validated outcome measures of RBC efficacy that assesses tissue oxygenation directly. With bleeding patients, the interpretation of post-transfusion Hb increment may be complicated by Hb loss due to bleeding and the dilutional effects of administering non-RBC-containing intravenous fluids. For these reasons, the study endpoints will be evaluated separately within the bleeding and non-bleeding subject populations.

An important secondary endpoint of the study is the incidence and clinical significance of antibodies to neoantigens formed as a result of amustaline and/or GSH binding to RBC surface membrane proteins or lipids during the pathogen reduction process. Naturally occurring antibodies with specificity to these RBCs have also been detected in surveillance studies of blood donors and patients transfused with conventional RBCs [10]. Treatment emergent antibodies specific to amustaline/GSH treated RBCs were observed with an earlier version of the amustaline/GSH pathogen reduction device, which was reconfigured to include a higher dose of GSH to further quench RBC side-reactions. The reconfigured amustaline/GSH device showed reduced immunogenicity in animal models and did not result in treatment-emergent antibodies in two randomized clinical trials in cardiac surgery patients and in transfusion-dependent β-thalassemia patients in Europe and Turkey [2, 6, 7]. In the United States-based ReCePI trial, [41] five of 159 test subjects (3.1%) developed treatment-emergent antibodies with specificity to amustaline/GSH RBCs. Most of these treatment-emergent and naturally occurring antibodies were neutralized by soluble acridine, suggesting specificity to acridine-containing adducts; [10] however, some antibodies have been detected that were not inhibited by acridine. To date, none of these antibodies have resulted in definite signs or symptoms of hemolysis and there have been no signs of decreased RBC lifespan. The five antibodies detected in the ReCePI study were detected 26–80 days post-surgery. Four of the five antibodies had negative DAT results (one was weakly positive with an amustaline/GSH-specific eluate). A monocyte monolayer RBC phagocytic assay (MMA) performed on fresh amustaline/GSH RBCs with high acridine surface density was non-reactive for three of the 5 subjects. Subjects had a mean exposure of 1–3 amustaline/GSH RBCs prior to developing antibodies. Flow cytometry tuned to detect acridine on RBC surface membranes was able to track persistent circulating amustaline/GSH-treated RBCs, indicating a lack of accelerated clearance [11].

The RedeS study is designed to exclude subjects with natural antibodies to amustaline/GSH RBCs at baseline and to detect and investigate the clinical significance of treatment emergent antibodies. The occurrence of a single subject with evidence of RBC hemolysis associated with an amustaline/GSH antibody would require a clinical hold with evaluation and DSMB and FDA approval to continue enrollment. No hemolytic antibodies have been reported at the time of this publication and none have been observed in any previous or on-going clinical study with amustaline/GSH RBCs. A small number (n = 4) of non-clinically significant, low titer antibodies reactive to the amustaline/GSH screening panel have been detected in the RedeS study to date. The study remains blinded and it is not known whether those subjects received Test or Control study RBCs. Documenting the rate and nature of (e.g., titer, immunoglobulin isotype) the humoral immune response to transfused RBCs as well as any potential clinical consequences (e.g., increased RBC clearance) will be critical to interpreting and understanding the potential clinical significance of these antibodies.

Other secondary efficacy endpoints include adjusted Hb consumption, the duration of study transfusion periods (days) in patients without active bleeding at baseline, and HbA clearance in SCD patients undergoing regular RCE. While comparable Hb consumption and transfusion support periods have been observed in prior clinical studies with amustaline/GSH RBCs, [7] little is known about Hb clearance in SCD patients on chronic simple transfusion therapy with amustaline/GSH RBCs compared to conventional RBCs (42). Likewise, HbA clearance in SCD patients receiving RCE therapy with amustaline/GSH RBCs has not been described previously.

This study design is associated with a number of potential limitations. In the absence of an acute epidemic or pandemic threat, enrollment and subject selection in transfusion medicine studies can be challenging due to competing trials and lack of patient awareness of transfusion medicine topics. Furthermore, the 6-month extension of this study has a significant on-study time commitment and potentially high number of study related activities (depending on the number of transfusions occurring during that period). Amendment 9 of the protocol limits the number of on-study transfusions to a maximum of ten. This change is designed to streamline recruitment in the 6-month extension arm and improve representativeness of the long-term cohorts as much as possible.

